## Abstract

Herniated nucleus pulposus (NP), one of the most common diseases of the spine, is surgically treated by removing the sequestered NP. However, intervertebral disc (IVD) defects may remain after discectomy, leading to inadequate tissue healing and predisposing patients to IVD degeneration. An acellular, bioresorbable, ultra-purified alginate (UPAL) gel (dMD-001) implantation system can be used to fill any IVD defects in order to prevent IVD degeneration after discectomy. This first-in-human pilot study aims to determine the feasibility, safety, and perceived patient response to a combined treatment involving discectomy and UPAL gel implantation for herniated NP. We designed a one-arm, double-centre, open-label, pilot trial. The study started in November 2018 and will run until a sample of 40 suitable participants is established. Patients aged 20–49 years, diagnosed with isolated lumbar IVD herniation and scheduled for discectomy represent suitable candidates. All eligible participants who provide informed consent undergo standard discectomy followed by UPAL gel implantation. The primary outcomes of the trial will be the feasibility and safety of the procedure. Secondary outcomes will include self-assessed clinical scores and magnetic resonance imaging-based measures of morphological and compositional quality of the IVD tissue. Initial outcomes will be published at 24 weeks. Analysis of feasibility and safety will be performed using descriptive statistics. Both intention-to-treat and per-protocol analyses of treatment trends of effectiveness will be conducted.

## Introduction

1

Herniated nucleus pulposus (NP), one of the most common diseases of the spine, is surgically treated by removing the sequestered NP. Discectomy is performed to remove intervertebral disc (IVD) material impinging on the nerve root, thereby alleviating pain. However, defects in the IVD may remain after discectomy, leading to inadequate tissue healing and predisposing patients to IVD degeneration. In addition, this open defect can serve as a point of egress for re-herniation, potentially resulting in recurrent symptoms and the need for further surgery [1]. To prevent re-herniation, surgeons are inclined to remove as much IVD material as possible, sometimes removing even material not displaced from within the annulus fibrosus (AF) [1]. While this practice may reduce re-herniation risk, it reportedly accelerates IVD degeneration, resulting in worse clinical outcomes and long-term back pain [[1], [2], [3]].

The regeneration capacity of IVDs is limited due to poor nutritional supply, low oxygen tension, acidic pH, low cell density, and cell viability and genetic predisposition [4,5]. Efforts to address this challenge have focused on biological repair of the whole IVD with NP and AF composite tissues. This is achieved using tissue engineering and regenerative medicine in combination with classical surgical procedures [[5], [6], [7]].

Although several basic research studies have demonstrated that alginate supports the reparative capacity of IVD [7,8], both naturally occurring and commercial-grade alginates contain mitogenic or cytotoxic impurities, which may induce foreign body reactions [9]. To explore the reparative capacity of alginate for tissue engineering in clinical applications while minimizing the risk of adverse effects, we previously developed a highly pure, biocompatible alginate with reduced endotoxicity (<50 EU/mL) [10]. An acellular bioresorbable ultra-purified alginate (UPAL) gel (dMD-001) implantation system was also developed for filling the IVD defect after discectomy, thus stimulating the ingrowth of reparative cells, promoting NP tissue formation, and preventing IVD degeneration. The feasibility of this treatment option, with formation of repair tissue and improvement of IVD water content, has been demonstrated in an animal model [11]. Thus, the next step was to design a first-in-human pilot study aiming to determine the feasibility, safety, and perceived patient response to a combined treatment involving discectomy and UPAL gel implantation for herniated NP. Should such a study indicate that the treatment may be effective, the collected data will be used to conduct a sample size calculation for a fully-powered trial.

## Methods

2

### Ethics

2.1

This study was designed in accordance with the Declaration of Helsinki and was approved by the ethics committees of Hokkaido University Hospital (approval number: H30-10) and Eniwa Hospital (approval number: dMD001-H1), as well as by the Japanese Pharmaceuticals and Medical Devices Agency (Japan). The trial will follow the Good Clinical Practice guidelines issued by the Japanese Ministry of Health, Labour and Welfare. Written informed consent is obtained from all patients before enrolment.

### Trial design

2.2

This first-in-human study is being conducted as a double-centre, open-label, pilot trial. An overview of the process of the trial is presented in Fig. 1 and Table 1. Protocol is version 1.0 and the protocol was fixed on July 5, 2018. The study started in November 2018 and recruitment of patients will end in September 2020 or will run until a sample of 40 suitable participants is established. And the last patient has been recruited in September 2020.

**Fig. 1 fig1:**
[figure not shown]
Study flow chart. MRI: Magnetic resonance imaging, UPAL: Ultra-purified alginate.

**Table 1 tbl1:** **Schedule of enrolment, intervention, assessment, and follow-up**.

	Study period					
	Enrolment	Operation	Post-operation			
Time point (week)	−1	0	1	4	12	24
**Enrolment**						
Eligibility screening	X	X				
Obtaining informed consent	X					
**Assessment**						
Recording demographic characteristics	X					
Physical examination/vital signs evaluation	X		X	X	X	X
Allergy test for sodium alginate (skin prick testing)	X					
Laboratory tests	X		X	X	X	X
Visual analog scale scoring for back pain and leg pain	X		X	X	X	X
Finger-to-floor distance test	X		X	X	X	X
Straight-leg-raising test	X		X	X	X	X
Modified Schober's test	X		X	X	X	X
Japanese Orthopaedic Association (JOA) scoring	X		X	X	X	X
36-item Short Form Health Survey	X		X	X	X	X
Oswestry Disability Index evaluation	X		X	X	X	X
Rolland-Morris disability questionnaire	X		X	X	X	X
JOA Back Pain Evaluation Questionnaire	X		X	X	X	X
Radiographic evaluation	X	X				
Magnetic resonance imaging evaluation	X					X
Reporting adverse events						
Recording medical/drug use history						

### Participants

2.3

Both pre-operative and surgical inclusion/exclusion criteria have been established for this trial. Specifically, the study will recruit participants with symptomatic herniated NP unresponsive to nonoperative care and considered candidates for nerve decompression and surgical excision of the herniated lumbar IVD fragments [1]. Clinical signs and symptoms, as well as magnetic resonance imaging (MRI) findings must corroborate the diagnosis of lumbar IVD herniation. Patients with previous lumbar surgery will not be considered for this trial. Furthermore, only patients who receive single-level discectomy will be considered eligible to receive UPAL gel implantation.

Upon completion of standard discectomy, the treating surgeon will assess the feasibility of AF re-approximation and make the final decision whether the patient will receive UPAL gel implantation and be officially enrolled in the study [1]. The complete inclusion/exclusion criteria are as follows [1].

Inclusion criteria.i.Candidate for lumbar discectomy.ii.Radiographic findings corroborating symptoms of IVD herniation.iii.Condition unresponsive to 6 consecutive weeks of therapy or experiencing acute/uncontrolled leg pain, defined as a score >80 on the 100-mm visual analog scale (VAS), in which higher scores representing worse pain correspond to worse pain.iv.Single-level lumbar IVD herniation.v.Persistent and predominant leg pain (score >40 on the 100-mm VAS)vi.Age between 20 and 49 years (inclusively).vii.Willingness to provide written informed consent, fill in all necessary questionnaires, and return for follow-up.

Exclusion criteria.i.Previous surgery involving a lumbar level.ii.Prior or planned spinal fusion involving a lumbar level.iii.Local kyphosis involving the affected disc level, evident on plain radiography of the lumbar spine in the flexion, neutral or extension position.iv.Spondylolisthesis or retrolisthesis above grade 1 at the affected level.v.Cauda equina syndrome.vi.Acute local or systemic infection.vii.Active malignancy or other similar comorbidities.viii.Current drug or alcohol dependency.ix.Current significant emotional disturbance.x.Current fracture, tumour, and/or deformity of the lumbar spine.xi.Current or planned pregnancy.xii.Currently enrolled in other research that could confound the results of the present trial.xiii.Presence of a metal implant or any other contraindication to MRI.xiv.Allergy to sodium alginate revealed upon skin prick testing.xv.Any other reason judged by an investigator or clinical trial doctor to render the candidate unsuitable for this clinical trial.

Eligible candidates will be treated at the Hokkaido University Hospital in Sapporo, Japan, or at Eniwa Hospital in Eniwa, Japan, depending on where the referring orthopaedic surgeons have formal accreditation. The treatment will include discectomy followed by UPAL gel implantation. The discectomy procedure is part of the accepted standard treatment of each participant but is not part of the present study. The discectomies will be performed by the referring surgeons and will not be performed by a single surgeon.

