#### Discectomy

2.5.1

All participants will undergo macroscopic discectomy for lumbar IVD herniation. These open procedures will be conducted using standard or tubular retractors, with or without the use of an operating microscope or loupes [1]. Manual, nonautomated methods for herniated IVD removal will be used exclusively, and no percutaneous methods will be applied [1]. To standardize the fenestration site for UPAL gel implantation, the procedures will involve an AF incision of 5 mm × 5 mm using a no. 15 surgical scalpel blade. In patients with transligamentous extrusion-type or sequestration-type herniated disc, the AF opening will be measured and reported. After the AF incision, we aim to remove as much disc material as possible. It will not be a limited discectomy. The technique used for discectomy will be at the discretion of the treating surgeon [1]. Whilst the surgeons’ preference and skill may confound the outcomes, this represents an acceptable limitation that has been purposefully allowed in order to facilitate recruitment of participants from across a wider orthopaedic community [12].

Stopping criteria before UPAL gel implantation.i.The AF incision for discectomy exceeds 5 mm × 5 mm (i.e., the diameter of the incision exceeds 5 mm).ii.The treating surgeon judges that AF re-approximation is not feasible or there is some other reason rendering the patient unsuitable for UPAL gel implantation such as a spinal fluid leak due to an incidental tear of the dura mater.iii.The volume of sterile, clinical-grade, normal saline delivered into the IVD defect exceeds 2.0 mL, indicating rupture of the AF.

If either of the above criteria for termination is met, no UPAL gel implantation will be conducted after the standard discectomy, and the patient will be excluded from the trial. The reason for stopping the UPAL gel implantation will be recorded.

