## Discussion

3

The main aim of this study is to examine the feasibility and safety of the combined treatment involving discectomy and UPAL gel implantation for herniated NP. In addition, measures of physical function scores, self-reported questionnaires for evaluating pain and health-related quality of life and MRI analysis for evaluating the IVD are performed to investigate perceived patient response to the procedure as secondary outcome measurement. Although surgeon can decide whether alginate implantation is feasible, resulting in a possible selection bias, the reason for stopping the implantation will be recorded and the feasibility will be analysed. This is a first-in-human pilot study designed to generate data that can be used to inform a future, large, randomised controlled trial should the intervention appear feasible and safe, and show trends of effectiveness. After the completion of this clinical trial, an observational study will be conducted as a historical control study in patients with lumbar disc herniation who have undergone discectomy only, using the same evaluation protocol as in this clinical trial.

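### The discectomy is declared outside the study yet prescribed as a trial intervention, so harms of the operation can drop out of the primary safety rate

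*Protocol article*

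**What the plan says.** **Outside the study.** Section 2.3 (Participants) of the protocol article states: "The discectomy procedure is part of the accepted standard treatment of each participant but is not part of the present study". The sentence just before it reads: "The treatment will include discectomy followed by UPAL gel implantation".

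**Inside the study.** Section 2.5.1 (Discectomy) sits under the heading Interventions and sets conditions for the operation. On the opening: "To standardize the fenestration site for UPAL gel implantation, the procedures will involve an AF incision of 5 mm × 5 mm". On the extent: "After the AF incision, we aim to remove as much disc material as possible. It will not be a limited discectomy". The Discussion gives the main aim as the "feasibility and safety of the combined treatment involving discectomy and UPAL gel implantation for herniated NP"; the Abstract and Introduction describe the object of study in the same way.

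**Enrolment and exclusion.** Consent is obtained before surgery (Table 1). Under section 2.3, the surgeon will, once the discectomy is complete, "make the final decision whether the patient will receive UPAL gel implantation and be officially enrolled in the study". Section 2.5.1 gives a spinal fluid leak from an incidental dural tear as an example of a reason to withhold the gel. A patient stopped at that stage is excluded from the trial, and the reason is recorded.

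**Safety outcome.** Section 2.6.1 makes safety a primary outcome and lists dural tear and spinal fluid leak among the serious adverse events to be recorded. Section 2.8 assesses safety as the rate of adverse events and reactions, without naming a denominator or a starting point.

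**The concern.** A trial cannot both prescribe an operation for the sake of its implant, evaluate the two together, and hold the operation outside the study. The reader needs to know which statement governs, because it decides which harms count.

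If the discectomy is outside the study, a harm that occurs during it, before enrolment, may be left out. If the combined treatment is what is evaluated, the same harm belongs to the primary safety outcome. The harm most clearly affected is on the protocol's own list: a dural tear with a leak during the discectomy. It can also be the event that removes the patient from the trial. Such losses run in one direction, since patients leave because they had a listed event, so the reported rate can only look better.

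This is a first-in-human study whose safety result is meant to inform a later randomised trial. A safety rate that means harms after successful implantation, but is read as harms of discectomy plus gel, would mislead that decision.

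**Working it through.** **1. The passages side by side (protocol article).**

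| Question | Pointing to outside the trial | Pointing to inside the trial |
|---|---|---|
| Is the discectomy part of the study? | 2.3: standard treatment, not part of it | 2.5.1: under Interventions, incision and extent set; Abstract, Introduction and Discussion: combined treatment evaluated |
| When does a patient enter? | 2.3: officially enrolled after the discectomy | Table 1: consent before the operation |
| Does an intraoperative leak count? | 2.5.1: gel withheld, patient excluded, reason recorded | 2.6.1: dural tear and spinal fluid leak are listed events |
| Over which patients? | 2.8: completion rate uses only patients who had the solution injected | 2.8: safety rate has no stated denominator |

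**2. The path of one patient.** A patient consents and has the discectomy; the dura is torn and leaks; the surgeon withholds the gel. Under 2.5.1 the patient is excluded, and under 2.3 was never officially enrolled. The stopping reason is kept, and the Discussion uses stopping reasons for the feasibility analysis. No passage carries the event into the safety rate. By contrast, section 2.5.2 keeps a patient stopped during implantation under safety assessment for up to 24 weeks. The gap is therefore specific to stops before implantation.

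**3. The plan's own figure.** Section 2.7 justifies 40 participants by a 95% probability of detecting events with 7.5% incidence. Read as the chance of seeing at least one:

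1 − (1 − 0.075)^40 = 1 − 0.925^40 = 1 − 0.044 = 0.956.

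The stated 95% is reproduced.

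**4. What exclusion could do to it (illustration).** Let a share *s* of the 7.5% events occur before implantation and lead to exclusion. The documents give no value for *s*, so the whole range is shown. With 40 patients operated on, the chance that at least one event is counted is 1 − (1 − 0.075(1 − *s*))^40.

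| Share *s* excluded (assumed) | Incidence still counted | Chance of counting at least one |
|---|---|---|
| 0 | 7.5% | 95.6% |
| 25% | 5.625% | 90.1% |
| 50% | 3.75% | 78.3% |
| 75% | 1.875% | 53.1% |
| 100% | 0 | 0% |

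If excluded patients are replaced until 40 have been implanted, the incidence among the implanted is 0.075(1 − *s*)/(1 − 0.075*s*). At *s* = 50% this is 0.0375/0.9625 = 3.9%, and the chance is 1 − 0.961^40 = 79.6%. Replacement hardly changes the picture.

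**The case against.** The best defence is that the discectomy is background care rather than the investigational product, carried out under conditions the trial sets. The article repeatedly calls it standard discectomy. On this view the sentence in 2.3 is loosely worded and nothing more. The safety list already contains plausible harms of the operation itself, and 2.8 does not restrict safety to gel-related events. The reason for every stop is recorded.

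Part of this stands. Section 2.3 nowhere says that discectomy harms are exempt from safety reporting, and leaks before implantation are not lost from the records. But a recorded stopping reason is not an event in the safety rate, and the background-care reading does not say when counting starts or over whom. The list in 2.6.1 and the exclusion in 2.5.1 still point in opposite directions.

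Two stronger readings are tempting, and the documents support neither:

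- **That the extent of removal is written two ways.** Only 2.5.1 states an extent; 2.3 is silent on it. The Introduction does say of maximal removal that "it reportedly accelerates IVD degeneration, resulting in worse clinical outcomes and long-term back pain", but it also says surgeons already tend to remove as much as they can, so usual practice may coincide with 2.5.1. The incision limit is enforced by a stopping criterion. Nor does "The technique used for discectomy will be at the discretion of the treating surgeon" contradict the fixed incision and extent, since the rest of the technique can remain free. Section 2.5.1 also discloses the surgeons' preference and skill as a confounder.
- **That a later comparison with discectomy alone would give false positive gel effects.** That comparison belongs to a separate observational study described in the Discussion. The extent of removal there is not stated, so any error rate would rest wholly on assumed shifts.

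**Conclusion.** The contradiction is in the current text and should be corrected. It bears on the primary safety outcome: as written, a dural tear or spinal fluid leak during the prescribed operation can be a listed serious adverse event and yet fall outside the reported rate.

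The size cannot be fixed from the documents. The drop from 95.6% to between 90.1% and 53.1% assumes a 7.5% incidence, 40 operated patients and an excluded share of 25% to 75%. It concerns only events that occur before implantation and stop it; events after implantation are unaffected. It also assumes that the exclusion rule is applied literally and that stopping reasons are not added back into the safety rate.

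The point does not show that harms have been hidden or that the operation varies with the section a surgeon follows. It shows that the safety estimand (which patients, and from when) is not settled by sections that disagree.

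**What to change.** Reconcile sections 2.3, 2.5.1, 2.6.1 and 2.8 so that one statement says whether the discectomy is part of the trial intervention. Which incision, extent or stopping rule is right is for the investigators and is not judged here.

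If section 2.5.1 stands:

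1. Remove from 2.3 the words that place the discectomy outside the study.
2. Count adverse events from the start of the discectomy in all consented patients operated on under the protocol, including those in whom implantation is stopped beforehand.
3. Report the safety rate over that denominator and, beside it, among implanted patients.

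If the discectomy is instead held outside the study, say so consistently, and describe the safety result as that of implanted patients rather than of the combined treatment. Events before implantation should then be tabulated separately.

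The cost is wording in a few sections and one more row in the safety table. Consent precedes surgery and stopping reasons are already recorded, so the operated patients can be identified. The downside is a slightly less favourable safety rate.

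Recording the extent of removal for the later discectomy-only study would be a useful option, but it does not correct an error in this protocol.

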### Recruitment

2.4

Candidates are being recruited from local orthopaedic hospitals. Patients with symptomatic herniated NP indicated for surgical treatment are invited to fill in a screening questionnaire to determine their eligibility. Patients who meet the inclusion criteria are contacted by one of the investigators to confirm their willingness to participate in the trial and arrange a baseline assessment, during which written informed consent is also obtained. Patients selected for the study may continue to use their prescribed medication for the duration of the trial. The type of medication and dosage used is recorded at the baseline assessment.

### Interventions

2.5

#### Discectomy

2.5.1

All participants will undergo macroscopic discectomy for lumbar IVD herniation. These open procedures will be conducted using standard or tubular retractors, with or without the use of an operating microscope or loupes [1]. Manual, nonautomated methods for herniated IVD removal will be used exclusively, and no percutaneous methods will be applied [1]. To standardize the fenestration site for UPAL gel implantation, the procedures will involve an AF incision of 5 mm × 5 mm using a no. 15 surgical scalpel blade. In patients with transligamentous extrusion-type or sequestration-type herniated disc, the AF opening will be measured and reported. After the AF incision, we aim to remove as much disc material as possible. It will not be a limited discectomy. The technique used for discectomy will be at the discretion of the treating surgeon [1]. Whilst the surgeons’ preference and skill may confound the outcomes, this represents an acceptable limitation that has been purposefully allowed in order to facilitate recruitment of participants from across a wider orthopaedic community [12].

Stopping criteria before UPAL gel implantation.i.The AF incision for discectomy exceeds 5 mm × 5 mm (i.e., the diameter of the incision exceeds 5 mm).ii.The treating surgeon judges that AF re-approximation is not feasible or there is some other reason rendering the patient unsuitable for UPAL gel implantation such as a spinal fluid leak due to an incidental tear of the dura mater.iii.The volume of sterile, clinical-grade, normal saline delivered into the IVD defect exceeds 2.0 mL, indicating rupture of the AF.

If either of the above criteria for termination is met, no UPAL gel implantation will be conducted after the standard discectomy, and the patient will be excluded from the trial. The reason for stopping the UPAL gel implantation will be recorded.

